### Treatment: DM control (allocation)

The subjects will receive oral hypoglycemic agents for glucose control; the type of agents will be determined by randomization. Patients using SGLT-2 inhibitors to control their serum glucose will be specified as the case group, while those using other hypoglycemic agents (e.g., metformin, meglitinides, sulfonylureas, DPP-4 inhibitors, GLP-1 receptor agonists, α-glucosidase inhibitors, and thiazolidinediones) to control their serum glucose will be classified as the control group. The number, type, and dosage of the agents will be individualized at the discretion of the physician in accordance with the 2021 ADA guidelines [31], considering factors such as the kidney function, age, and cardiovascular status.

### Follow-up and detection of AF recurrence

After their recruitment, the participants will receive baseline and evaluation studies under scrutiny, which include history taking, physical examination, blood sampling, urine sampling, 12-lead ECG, 24-h Holter ECG, TTE, EHRA, EQ-5D, and SF-12. The follow-up schedule will begin with the prescription of oral hypoglycemic agents (Table 5). During each intervention, the following steps were conducted: (1) history taking for the review of AF and DM status, adverse events, and other specific illnesses on every visit; (2) physical examination to evaluate any DM complication, AF, NYHA score, neurologic exam, systolic and diastolic blood pressure; (3) blood sampling for CBC, BUN/Cr, electrolyte, coagulation profile, HbA1c, fasting glucose, AST/ALT, lipid battery, and NT-proBNP; (4) urine sampling for dip stick urinalysis with microscopy and measuring proteinuria (especially for albuminuria); and (5) TTE to measure the LA size and left ventricular ejection fraction (LVEF). Any other additive assessing procedure may be conducted and recorded during the clinical course of the patients.

**Table 5 pone.0280359.t005:** Data-collection requirements.

Investigation	Baseline	3M	6M	9M	12M
Inclusion/Exclusion criteria	X				
Medical History	X	X	X	X	X
Physical Examination	X	X	X	X	X
12-lead ECG	X	X	X	X	X
24-h Holter ECG*	X	X	X	X	X
Blood, Urine sample	X				X
Transthoracic Echocardiography (TTE)	X				X
NT-proBNP	X				X
EHRA Score	X	X	X	X	X
EQ-5D, SF-12	X				X
Adverse Events History**		X	X	X	X

*Patients with an ablation (RFA or 4PVI) will be monitored every 3 months that point on for an additional year.

**To evaluate adverse events, any suitable diagnostic investigation can be performed.

Abbreviations. ECG, electrocardiogram; NT-proBNP, N-terminal pro-B-type natriuretic peptide; EHRA, European Heart Rhythm Association; EQ-5D, EuroQol-5 Dimension; SF-12, Short Form-12 Health Survey Questionnaire.

During patient monitoring, if AF recurs and the patient complains of its symptoms, RFA or cryoablation (4PVI) will be performed at the discretion of the physician in accordance with the 2020 ESC [30] 2019 AHA/ACC/HRS guidelines [20] for AF. For patients with ablation, 24-h Holter ECG monitoring every 3 months for an additional year will be performed from that point on. If severe adverse events occur, the patient will be excluded from the study after a committee meeting. The main concern of the review is the recurrence of AF, which is the primary outcome of this trial.

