### Study design and participants

This is a multicenter study with a prospective, open, blinded endpoint design (Fig 1). It is a 1:1 randomized and controlled study that compares the rhythm control effect of SGLT-2 inhibitor therapy to other oral hypoglycemic agents in patients with AF and DM (Fig 2).

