### Statistical plan, sample size, and power determination

In this study, 716 patients will be enrolled from 7 tertiary medical centers. The sample size was determined based on the primary outcome, i.e., the SGLT-2 inhibitors should show 40% reduction in AF after a year of treatment [32] and 50% of AAD users should step up to the ablation therapy [33,34]. Assuming 10% follow-up loss, the sample size of 716 patients (358 in each group) is expected to achieve 80% power and an alpha-level of 5% to detect the difference. The study is powered to demonstrate the superior additive effect of SGLT-2 inhibitors over other hypoglycemic agents using the Chi square method. AF recurrence rate and ratio of sinus rhythm on 24-h holter EKG will be analyzed using Chi square test, and left atrial size, NT-pro BNP and quality of life (AFEQT) score on 12-month final follow-up will be analyzed by student t-test. Disease-free survival and overall survival during the follow-up period will be calculated using Kaplan-Meier method. Mono-variable and multi-variable cox regression analysis will be used to calculate hazard ratio of SGLT-2 group.

To reduce the selection bias, all subjects will be randomized to allocate the hypoglycemic agents according to random number table. Missing data is planned to be controlled using multiple imputation.

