### Study status and organization

Ewha Womans University Mokdong Hospital is responsible for this trial, and the Institutional Review Board (IRB) of Ewha Womans University Mokdong Hospital approved this research plan, including the written consent form (S2, S3 and S4 File). In addition to Ewha Womans University Mokdong Hospital, at least seven other tertiary hospitals in South Korea are now preparing for IRB approval of each hospital with the same research plan.

This study complied with the fundamental spirit of the clinical trial management standards of the Helsinki Declaration (revised 2013) and the International Conference on Harmonisation of Technical Requirements for Registration of Pharmaceuticals for Human Use–Guidelines for Good Clinical Practice (ICH-GCP). The study was initiated after approval of the IRB in each medical center, and after approval, centers recruited patients and the therapies were administered following the appropriate study protocol and clinical standards.

Patients who met the inclusion criteria and voluntarily agreed to enroll in the study provided written informed consent, which was reviewed and approved by the IRB of each participating hospital after sufficient explanation about the research process. Personal identifiers were kept confidential by the researcher, and the research data was recorded with initials and research subject identification information was coded.

All adverse events reported by the subjects during a 3-month follow-up were reported at meetings between researchers four times a year and evaluated by an independent committee. Interruption of participation was decided when the above adverse reaction was a considerable side effect of the SGLT-2 inhibitors (dapagliflozin and empagliflozin), as informed by the Ministry of Food and Drug Safety, or was a serious adverse event unrelated to causality.

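### Patients with severe adverse events leave the study itself, under two unreconciled rules, one of which names only SGLT-2 side effects, and nothing keeps them in follow-up

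*Protocol article*

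**What the plan says.** Two passages of the protocol article govern removal after an adverse event.

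- **Follow-up and detection of AF recurrence:** "If severe adverse events occur, the patient will be excluded from the study after a committee meeting". The sentence names no arm and no drug. It removes the patient from the study, not only from the study drug.
- **Study status and organization:** "Interruption of participation was decided when the above adverse reaction was a considerable side effect of the SGLT-2 inhibitors" (dapagliflozin and empagliflozin are named), "or was a serious adverse event unrelated to causality". The first limb concerns SGLT-2 inhibitors only. The second covers both arms, and its wording on causality is most naturally read as regardless of cause.

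Three other passages bear on the point.

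- **Treatment: DM control (allocation)** says that "the type of agents will be determined by randomization", then describes the arms by use: "Patients using SGLT-2 inhibitors to control their serum glucose will be specified as the case group", with patients on other agents "to control their serum glucose will be classified as the control group".
- **Study design and participants:** "This is a multicenter study with a prospective, open, blinded endpoint design". Patient and physician therefore know the arm when events are reported and attributed.
- **Statistical plan, sample size, and power determination** plans a chi-square test on AF recurrence, with Kaplan-Meier and Cox analyses, and says: "Missing data is planned to be controlled using multiple imputation". It does not say whether this covers patients removed for adverse events.

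**The concern.** Stopping a drug and leaving a trial are different events. The first is a clinical decision; the second ends data collection. The article joins them: a severe adverse event ends participation, and no passage provides for further Holter recordings, visits or safety checks.

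The loss occurs after randomisation and may be unequal. A considerable but non-serious side effect of an SGLT-2 inhibitor can end participation, while the text gives no such trigger for a comparable side effect of a sulfonylurea, a thiazolidinedione or another comparator. In an open-label trial, attributing an event to the drug is itself open to knowledge of the arm. The discussion says physicians will be recommended to use maximum tolerable SGLT-2 doses, so stopping for intolerance in that arm is a realistic prospect.

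Two things are at stake. The primary comparison could be distorted if those removed differ in recurrence risk from those who stay. Later safety events in the removed patients would also go unseen, although the trial sets out to evaluate safety. An analysis plan cannot recover outcomes that the protocol stopped collecting.

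**Working it through.** **1. The two rules side by side**

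| | Follow-up and detection of AF recurrence | Study status and organization |
|---|---|---|
| Trigger | severe adverse event | considerable SGLT-2 side effect, or serious adverse event |
| Arms reached | both | first limb: SGLT-2 only; second limb: both |
| Consequence | excluded from the study | interruption of participation |
| Follow-up afterwards | not provided for | not provided for |

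Triggers and consequences are worded differently, and neither passage refers to the other. The textual asymmetry is confined to SGLT-2 side effects that are considerable but not serious.

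**2. What the documents give in numbers**

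There is no exclusion rate, no recurrence risk for removed patients and no control-arm recurrence rate, so there is no plan figure to reproduce for this point. The planned 716 patients (358 per arm) include 10% for follow-up loss. That is an overall allowance, not an adverse-event exclusion rate, and it says nothing about imbalance between arms.

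**3. Illustration, all rates assumed**

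Take no drug effect and a true recurrence of p = 0.35 in both arms. Remove a fraction x of an arm, with recurrence risk q among those removed, and delete them from the analysis:

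observed risk = (p − x·q) / (1 − x)

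The fraction removed in control is set at about a third of that in the SGLT-2 arm.

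| x, SGLT-2 | x, control | q | SGLT-2 | Control | Difference (points) |
|---|---|---|---|---|---|
| 0.05 | 0.017 | 0.35 | 35.0% | 35.0% | 0 |
| 0.05 | 0.017 | 0.45 | 34.5% | 34.8% | 0.4 |
| 0.05 | 0.017 | 0.60 | 33.7% | 34.6% | 0.9 |
| 0.08 | 0.027 | 0.70 | 32.0% | 34.0% | 2.1 |

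Third row: (0.35 − 0.05 × 0.60)/0.95 = 0.320/0.95 = 33.7%, and (0.35 − 0.017 × 0.60)/0.983 = 0.3398/0.983 = 34.6%.

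Fourth row: (0.35 − 0.08 × 0.70)/0.92 = 0.294/0.92 = 32.0%, and (0.35 − 0.027 × 0.70)/0.973 = 0.3311/0.973 = 34.0%.

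For scale, a 40% reduction from 35% would be 0.40 × 35 = 14 points.

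**4. Effect on the false-positive rate**

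Here removed patients have r times the recurrence risk of those who stay, so observed risk = p / (1 − x + x·r). The test is a two-sided 5% two-proportion test with 358 per arm before removal.

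| True recurrence | Removed, SGLT-2 vs control | Type I error, r = 1 | r = 1.5 | r = 2 |
|---|---|---|---|---|
| 50% | 5% vs 2% | 5.0% | 5.4% | 6.6% |
| 50% | 10% vs 2% | 5.0% | 7.8% | 15.2% |
| 20% | 5% vs 2% | 5.0% | 5.1% | 5.4% |
| 20% | 10% vs 2% | 5.0% | 5.7% | 7.6% |

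The 15.2% corner is an extreme case: 0.50/1.10 = 45.5% against 0.50/1.02 = 49.0%, or 3.6 points.

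**5. Missing data**

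Standard multiple imputation assumes that, given the observed data, those with missing outcomes resemble those without. Removal for toxicity, under a trigger written for one arm, makes that doubtful. The observed data cannot test it, because the outcomes after removal were never recorded.

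**The case against.** The strongest reply has five parts.

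- **The rule is not SGLT-2-only.** The exclusion sentence is neutral between arms, and the interruption rule has a limb for serious events in either arm. This stands. The asymmetry is partial, and how the two rules combine is unclear rather than settled.
- **The groups are as randomised.** A reader might infer from the wording about patients using each drug class that this is an as-treated comparison, in which a patient who switches changes group. The documents do not support that. The preceding sentence sets the agent type by randomisation, the section heading says allocation, and nothing reclassifies switchers. The text is only silent on what happens after a stop or switch, which is worth a clarifying phrase.
- **The harms are still reported.** The triggering event goes to an independent committee, so a claim that SGLT-2 harms are understated outright would go too far. Only events after removal could be lost.
- **Data before removal may be kept.** The article does not say they are deleted, and the Kaplan-Meier and Cox analyses could use them. The illustration deletes removed patients entirely, so it overstates the effect if earlier recurrences count.
- **Details may sit in documents not shown.** Analysis sets commonly belong in the full protocol or analysis plan, so a missing intention-to-treat label alone would be no finding. This point rests on the explicit removal rules, which the article does state.

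**Conclusion.** The point holds in limited form. As written, the article removes patients from the study after severe adverse events and interrupts participation under a second rule with an SGLT-2-specific limb. It leaves the two unreconciled and provides no follow-up for those removed. Outcomes after randomisation would then be lost, possibly more often in the SGLT-2 arm.

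The direction of any bias is conditional. It favours SGLT-2 inhibitors only if more patients are removed from that arm and those removed have above-average recurrence risk. With no drug effect, 35% recurrence, 5% to 8% removed from the SGLT-2 arm and about a third of that from control, and complete deletion, the spurious difference runs from 0 (average risk) to about 2 points (70% risk). None of these rates is in the documents. A reader might take the 10% loss allowance as evidence that removals of this size are expected; it is not.

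The size is therefore uncertain and probably modest against the planned effect. The correction is still worth making in the protocol, because uncollected outcomes cannot be restored at the analysis stage.

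**What to change.** 1. **Reconcile the two removal passages** (Follow-up and detection of AF recurrence; Study status and organization). State separately what leads to stopping or changing a study drug and what leads to leaving the study, and how the two rules relate.
2. **Use one follow-up rule for both arms.** A patient who stops or changes study drug for any reason stays in all scheduled Holter, visit and safety follow-up unless consent is withdrawn. This must include the 12 months after ablation where it applies. A cut-off at month 12 from enrolment would conflict with the article's own post-ablation schedule and could lose primary-outcome data.
3. **Analyse as allocated.** The primary comparison includes all randomised patients in their allocated arm. Any on-treatment analysis is a sensitivity analysis.
4. **Clarify the allocation section:** the case and control groups are the groups as randomised.

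The clinical decision to stop a drug is untouched, and the sample size stays at 716. The cost is protocol wording, continued routine visits for a few patients, and some dilution of the effect when patients stop or change drug.

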### Statistical plan, sample size, and power determination

In this study, 716 patients will be enrolled from 7 tertiary medical centers. The sample size was determined based on the primary outcome, i.e., the SGLT-2 inhibitors should show 40% reduction in AF after a year of treatment [32] and 50% of AAD users should step up to the ablation therapy [33,34]. Assuming 10% follow-up loss, the sample size of 716 patients (358 in each group) is expected to achieve 80% power and an alpha-level of 5% to detect the difference. The study is powered to demonstrate the superior additive effect of SGLT-2 inhibitors over other hypoglycemic agents using the Chi square method. AF recurrence rate and ratio of sinus rhythm on 24-h holter EKG will be analyzed using Chi square test, and left atrial size, NT-pro BNP and quality of life (AFEQT) score on 12-month final follow-up will be analyzed by student t-test. Disease-free survival and overall survival during the follow-up period will be calculated using Kaplan-Meier method. Mono-variable and multi-variable cox regression analysis will be used to calculate hazard ratio of SGLT-2 group.

To reduce the selection bias, all subjects will be randomized to allocate the hypoglycemic agents according to random number table. Missing data is planned to be controlled using multiple imputation.

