## Abstract

SGLT-2 inhibitor, traditionally used for glycemic control, has several beneficial effects that can help manage heart failure (HF). SGLT-2 inhibitors reduce the risk of cardiovascular mortality in patients with HF. As atrial fibrillation (AF) is closely associated with HF and diabetes mellitus (DM) is a risk factor for AF, we assume that SGLT-2 inhibitors will also show therapeutic benefits regarding AF, especially for rhythm control. This trial has a multicenter, prospective, open, blinded endpoint design. It is a 1:1 randomized and controlled study. A total of 716 patients who are newly diagnosed of AF and DM within 1 year will be enrolled from 7 tertiary medical centers. The trial is designed to compare the effects of SGLT-2 inhibitors and other oral hypoglycemic agents on atrial rhythm control in patients with AF and DM. The primary outcome is the recurrence of AF within a year (including post-antiarrhythmic drugs (AAD) or ablation). The secondary outcomes are the ablation rate within a year, change in AF burden, size of the left atrium, NT-proBNP, the AF symptom score, and the quality of life. This trial will prospectively evaluate the effect and safety of SGLT-2 inhibitors on AF rhythm control in patients with DM. It will provide an invaluable dataset on rhythm control in AF with DM for future studies and offer novel information to assist in clinical decisions. (BEYOND trial, ClinicalTrials.gov number: NCT05029115. https://clinicaltrials.gov/ct2/show/NCT05029115).

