As dilatation of the left atrium (LA) is associated with AF in both pathophysiologic and prognostic perspectives, we will use the LA size as a secondary outcome. Left atrial remodeling induces electrical modification, which is associated with AF. LA structural remodeling is characterized by atrial dilatation [24]. An increase in the LA size at baseline is associated with progressive LA enlargement and AF recurrence. Hence, the LA size can be considered a prognostic factor for spontaneous conversion of AF [25]. As an indicator of LA dilatation, the left atrial diameter (anterior–posterior) will be measured by transthoracic echocardiography (TTE) at baseline and 12-month follow-up visit [26]. N-terminal pro-B-type natriuretic peptide (NT-proBNP) is often elevated in AF and is higher in severe AF [27,28]. As it is a significant secondary outcome, we will measure the level of NT-proBNP in blood and compare their values in the two groups at baseline and 12-month follow-up visit.

The symptom score is compared by using the EHRA score. It is measured at baseline, 3-, 6-, 9-, and 12-month of follow-up visits. The ratio of asymptomatic participants will be compared between the two groups. To compare the quality of life between the two groups, EuroQoL five-dimensional instrument (EQ-5D, www.euroqol.org) and SF-12 (a shortened version of SF-36, www.sf-36.org) Health Survey will be used, and assessments will be conducted between the data on baseline and 12-month follow-up visit.

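### The primary chi-square test leaves out baseline left atrial size, which the protocol itself links to AF recurrence and measures in every patient; prespecified adjustment would give a modest, cheap gain in precision

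*Protocol article*

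**What the plan says.** The Abstract defines the endpoint: "The primary outcome is the recurrence of AF within a year (including post-antiarrhythmic drugs (AAD) or ablation". The section on the statistical plan, sample size and power assigns it to a test, "AF recurrence rate and ratio of sinus rhythm on 24-h holter EKG will be analyzed using Chi square test", and bases the power on the same test: "The study is powered to demonstrate the superior additive effect of SGLT-2 inhibitors over other hypoglycemic agents using the Chi square method". Neither sentence names a covariate or a stratum.

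The Secondary outcomes section, when it justifies LA size as an outcome, states: "An increase in the LA size at baseline is associated with progressive LA enlargement and AF recurrence". LA diameter "will be measured by transthoracic echocardiography (TTE) at baseline and 12-month follow-up visit". The follow-up section lists "12-lead ECG, 24-h Holter ECG, TTE, EHRA, EQ-5D, and SF-12" among the baseline studies, and Table 5 marks echocardiography and Holter at baseline for all participants.

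On allocation, the statistical section says that "all subjects will be randomized to allocate the hypoglycemic agents according to random number table". On adjusted analysis it says only: "Mono-variable and multi-variable cox regression analysis will be used to calculate hazard ratio of SGLT-2 group". That sentence follows the one on survival endpoints, and AF-free survival is listed as a secondary outcome.

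**The concern.** When a baseline variable predicts a binary outcome, part of the outcome variation can be explained before the arms are compared. An unadjusted test leaves that part in the error term. The protocol supplies both conditions for doing better: it says that LA size is prognostic for this endpoint, and it measures LA size before treatment in every patient. It then fixes a primary test that cannot use the measurement.

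At stake is efficiency. The trial is planned at 80% power, so a few points gained without extra patients or procedures are worth having. Adjustment also corrects the estimate for whatever LA imbalance randomisation happens to produce.

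**Working it through.** **Inputs from the statistical section.** 358 per arm, 10% loss, so 0.9 × 358 = 322 evaluable per arm; 80% power; 5% alpha (taken as two-sided, because the side is not stated); 40% reduction (taken as a risk ratio of 0.6).

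**Not given.** The control-arm recurrence rate and the strength of the LA–recurrence association. Both are assumptions below.

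**Step 1: the plan's own figure.** 716 cannot be reproduced without a control rate, so I solved for one. With p₀ = 0.203, p₁ = 0.6 × 0.203 = 0.1218 and p̄ = 0.1624:

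n = [1.96√(2p̄(1−p̄)) + 0.8416√(p₀(1−p₀) + p₁(1−p₁))]² / (p₀−p₁)² = 322.7, so 323 per arm.

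Dividing by 0.9 gives 359 per arm, against the stated 358. Control rates of about 0.199 to 0.208 come similarly close.

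**Step 2: power of the chi-square test at 322 per arm.**

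Power = Φ{[0.0812√322 − 1.96√(2 × 0.1624 × 0.8376)] / √(0.1618 + 0.1070)} = Φ{(1.457 − 1.022)/0.518} = Φ(0.839) = 79.9%.

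**Step 3: gain from adjustment.** Take LA size as a standard normal covariate X in a logistic model with slope b per SD. Set the intercepts so that the average risks stay at p₀ and p₁, and let m₀(X) and m₁(X) be the risks given X. The variance of the standardised risk difference relative to the unadjusted one is

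r = {2E[m₀(1−m₀)] + 2E[m₁(1−m₁)] + Var(m₁−m₀)} / {2p₀(1−p₀) + 2p₁(1−p₁)}.

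Example, odds ratio 2.0 per SD: r = (0.5034 + 0.0012)/0.5375 = 0.939. Adjusted power is the Step 2 formula evaluated at 322/r, the equivalent total is 716 × r, and the gain in effective patients is 1/r − 1.

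| Odds ratio per SD (slope b) | r | Gain in effective patients | Power, unadjusted → adjusted | Total for the same power |
|---|---|---|---|---|
| 1.2 (0.18) | 0.996 | 0.5% | 79.9% → 80.1% | 713 |
| 1.5 (0.41) | 0.978 | 2% | 79.9% → 80.8% | 701 |
| 1.65 (0.5) | 0.967 | 3% | 79.9% → 81.2% | 693 |
| 2.0 (0.69) | 0.939 | 7% | 79.9% → 82.4% | 673 |
| 2.23 (0.8) | 0.920 | 9% | 79.9% → 83.1% | 659 |
| 2.5 (0.92) | 0.898 | 11% | 79.9% → 84.0% | 644 |
| 2.72 (1.0) | 0.882 | 13% | 79.9% → 84.7% | 632 |

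A simulation of 4,000 trials at an odds ratio of 2.0 gave 78.7% power for the chi-square test and 81.2% for adjusted logistic regression, which agrees with the asymptotic gain.

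**Step 4: sensitivity to the control rate.**
- If the 50% step-up assumption means that only half of each arm is analysed (161 per arm), a control rate near 0.35 fits 716. Odds ratios of 1.2 to 2.5 then take power from 80.2% to between 80.4% and 85.4%.
- With 35% v 21% and all 322 per arm, unadjusted power is already about 98%, and adjustment adds about one point or less.

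**Step 5: chance imbalance.** The difference in mean LA size between arms has standard error √(2/322) = 0.079 SD, so an unlucky imbalance is about 1.96 × 0.079 = 0.154 SD. At an odds ratio of 2.0 this shifts the log-odds by 0.154 × 0.693 = 0.107. Multiplied by the average m(1−m) of 0.5034/4 = 0.126, that is about 1.3 percentage points, against a planned difference of 8.1 points. This is the same precision loss seen from another side, not an additional one.

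**The case against.** The strongest reply is that nothing here is an error. An unadjusted chi-square test is valid for a binary outcome in a 1:1 randomised trial, and the power calculation and the analysis use the same test. LA size is mentioned to justify a secondary outcome, and covariate lists usually belong in the analysis plan, which is not shown. Validity and consistency stand. The point about the analysis plan stands only in part: the article is not silent on the primary test but fixes it, and adjustment would be a different primary analysis rather than a detail of this one. Silence on stratified allocation, by contrast, is ordinary in a condensed article and no fault is found there.

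A second reply is that adjustment is already planned through the multivariable Cox regression. It must be acknowledged, and it would be wrong to say that the plan contains no adjusted estimate. But its covariates are unnamed and it sits with the survival endpoints, so the primary test remains unadjusted.

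A third reply is that the gain is unquantified and may be trivial. This stands. The article supports the direction of the LA association, not its strength, and it does not call baseline Holter AF a predictor of the primary outcome.

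Two stronger readings are tempting. A reader might infer that the chi-square result would be biased or its error rate inflated; randomisation rules that out, because chance imbalance is already covered by the test's error rate. A reader might also infer a large gain by taking 35% v 24% with 322 per arm, where slopes of 0.5, 0.8 and 1.0 give 5%, 12% and 18% more effective patients and power goes from 87% to 88–92%. That contrast is a relative reduction of 11/35 = 31%, not the stated 40%, so it is not the trial as planned.

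**Conclusion.** The point holds as an inexpensive efficiency improvement. The stated primary analysis is valid but leaves unused a baseline variable that the protocol calls prognostic and collects in everyone.

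At the control rate that reproduces 716 (about 20% v 12%), the gain is under one power point for an odds ratio of 1.2–1.5 per SD, and about 1 to 5 points for slopes of 0.5–1.0. The top of that range needs an odds ratio of about 2.7 per SD, from LA size alone or from several baseline predictors together.

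All of these figures assume a control rate and an association strength that the article does not give, a two-sided 5% test, and a 40% reduction read as relative. The missing control rate is a separate and larger matter.

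**What to change.** Before any outcome data are seen, prespecify the primary analysis as a logistic regression of 12-month AF recurrence on allocated arm and baseline LA diameter (continuous). Baseline Holter AF and centre may be added, with small centres pooled by a stated rule. Report the standardised risk difference with its confidence interval, and keep the chi-square test as supportive. The sample size can stay at 716, because adjustment is not expected to lower power.

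The cost is a sentence or two in the analysis plan, with no new patients, visits or procedures. The downside is small: the covariates and their form must be fixed in advance, and missing baseline values need a stated method. The multiple imputation already planned could be extended to them.

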### Secondary outcomes

Secondary outcomes are listed in Table 1. AF-free survival will be compared between the two groups as the first of the secondary outcome, analyzed using the Kaplan–Meier method, and documented on curve. AF burden at 3-month follow-up visit, 12-month follow-up visit in those who did not step up and used AAD only for rhythm control, immediately before trying ablation, and at 12-month follow-up visit in those who stepped up and underwent ablation in both the SGLT-2 inhibitor group and the control group will be compared. AF burden is defined as the atrial fibrillation time percentage documented on 24-h Holter ECG [22]. Ablation rate, which is the percentage of patients undergoing ablation, within a year will also be compared between the two groups to identify the efficacy of symptom and rhythm control using SGLT-2 inhibitors. Sinus rhythm is considered stable when either a standard ECG or a 24-h Holter ECG showed no episode of clinically relevant arrhythmia, including AF, at the time of check-up [23]. The proportion of participants with stable sinus rhythm in all participants, regardless of with or without ablation, is compared between the two groups at baseline, 6-, and 12-month follow-up visits.

**Table 1 pone.0280359.t001:** Secondary outcomes.

• Rhythm control • AF-free survival • AF burden at • 3-month F/U visit, 12-month F/U visit in those who did not step up to session 2 • Immediately before trying ablation, 12-month F/U visit in those who stepped up to session 2 • Percentage of patients undergoing ablation within a year • Sinus rhythm maintenance* • Diameter of LA • NT-proBNP • Symptom score (EHRA score) • Quality of life (EQ-5D, SF-12)

*Defined as the absence of clinically relevant arrhythmia (e.g., AF, AFL, sustained VT, and VF).

AF, atrial fibrillation; LA, left atrium; F/U, follow up; NT-proBNP, N-terminal pro-B-type natriuretic peptide; EHRA, European Heart Rhythm Association; EQ-5D, EuroQol-5 Dimension; SF-12, Short Form-12 Health Survey Questionnaire; AFL, atrial flutter; VT, ventricular tachycardia; VF, ventricular fibrillation.

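### The quality-of-life test names the AFEQT, which no outcome list or visit schedule contains, while the scheduled EQ-5D and SF-12 have no stated test

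*Protocol article*

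**What the plan says.** The section on the statistical plan, sample size and power gives one rule for quality of life: a Student t-test on the "quality of life (AFEQT) score on 12-month final follow-up". It mentions neither the EQ-5D nor the SF-12.

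The sections that define and schedule the outcome name other instruments:

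- Table 1, under Secondary outcomes, lists "Quality of life (EQ-5D, SF-12" and no other quality-of-life instrument.
- The text of the same section says that the groups will be compared with the "EuroQoL five-dimensional instrument (EQ-5D, www.euroqol.org) and SF-12", and that "assessments will be conducted between the data on baseline and 12-month follow-up visit".
- The section on follow-up and detection of AF recurrence ends its list of baseline and evaluation studies with "12-lead ECG, 24-h Holter ECG, TTE, EHRA, EQ-5D, and SF-12".
- Table 5 has a single quality-of-life row, for EQ-5D and SF-12, marked at baseline and 12 months.

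The abbreviation lists under Tables 1 and 5 expand EQ-5D and SF-12. Neither contains AFEQT.

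**The concern.** An analysis rule works only if it names a variable that the trial sets out to record. Here the rule and the schedule point to different questionnaires. A site that follows Table 5 has no instruction to administer the AFEQT at any visit. A statistician who follows the statistical section finds no rule for the two questionnaires that the site did administer.

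Quality of life is a named secondary outcome and appears in the abstract. It is reported by patients who know their treatment in an open-label trial. Its instrument and comparison should therefore be settled in advance and not repaired at analysis. A statistical analysis plan can add detail to a stated rule. It cannot supply data from a questionnaire that no visit called for.

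**Working it through.** No figure is involved, so the check is a comparison of places in the protocol article.

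| Place | Instrument | Time points | Test |
|---|---|---|---|
| Table 1 | EQ-5D, SF-12 | none given | none |
| Secondary outcomes, text | EQ-5D, SF-12 | baseline and 12 months | none |
| Follow-up section, text | EQ-5D, SF-12 | baseline and evaluation studies | none |
| Table 5 | EQ-5D, SF-12 | baseline and 12 months | none |
| Statistical section | AFEQT | 12 months | Student t-test |

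**Step 1: instrument.** Four places agree on EQ-5D and SF-12. The fifth, the only one that states a test, names the AFEQT. No instrument has both a scheduled collection and a stated test.

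**Step 2: is the mismatch peculiar to quality of life?** The same sentence of the statistical section also covers left atrial size and NT-proBNP. Both are in Table 1, and Table 5 schedules both at baseline and 12 months (left atrial size through echocardiography). For these two, the sentence matches the schedule. Only the quality-of-life item does not.

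**Step 3: does another clause schedule the AFEQT?** The nearest candidate is in the follow-up section: "Any other additive assessing procedure may be conducted and recorded during the clinical course of the patients". This is a general permission. It names no questionnaire and fixes no visit, so it does not provide for the AFEQT in both groups at month 12.

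**Step 4: contrast.** The outcome definition uses baseline and 12-month data. The statistical section uses the 12-month score alone. These remain different comparisons even if AFEQT is only a wrong label, so changing the name would not fully reconcile the two sections.

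**Step 5: can one analysis serve both descriptions?** Yes. An analysis of covariance of the 12-month score on group and baseline score compares the groups at 12 months, as the statistical section intends, and uses the baseline value, as the outcome definition intends. With correlation r between the baseline and 12-month scores, it multiplies the residual variance by about 1 − r² relative to the 12-month score alone. The article gives no r, so no size is claimed for the gain. The baseline EQ-5D and SF-12 it needs are already in Table 5.

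**The case against.** The strongest reply is that this is a labelling slip. The outcome in the statistical section is a quality-of-life score with AFEQT in parentheses, and the time point and test are fixed. Put EQ-5D and SF-12 in the parentheses and the same t-test can be run on data already scheduled. Much of this stands: the repair is easy, and to say that quality of life cannot be analysed at all would go too far. It does not remove the contradiction, because the article does not show which instrument was meant, and the mismatch in contrast would remain.

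A second reply is that an unadjusted t-test on 12-month scores is valid between randomised groups. That is also correct. Baseline adjustment is proposed because it reconciles the two sections at no cost in data, not because the t-test is invalid. It would leave left atrial size and NT-proBNP on the t-test unless they were handled in the same way.

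Three stronger readings are tempting, and the document supports none of them:

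- **No patient will have an AFEQT score.** The article shows only that the AFEQT is not scheduled. The clause on additional assessments does not exclude it, and the supplementary files that the article cites are not shown.
- **The team will choose among several EQ-5D and SF-12 scores after seeing the results, and so inflate the false-positive rate.** Nothing in the text suggests such a choice. Any figure for it would need a number of scores and a correlation that the article does not give. Which component score leads is commonly left to the statistical analysis plan.
- **Lost AFEQT baselines spoil the planned test.** The test as stated uses the 12-month score only and needs no baseline. A missing baseline would matter only if the baseline-based comparison in the outcome definition were applied to the AFEQT.

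**Conclusion.** The point holds as a contradiction within the protocol article. The stated test is attached to an unscheduled instrument, the scheduled instruments have no stated test, and the two descriptions of the comparison differ in their use of baseline. This is a conflict between rules that the article itself states, so it is not detail left to an unseen analysis plan.

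Its reach is limited to one secondary outcome. The primary outcome, its chi-square test and the sample size of 716 (358 per group) do not depend on it. It should be corrected, but it does not threaten the trial's main conclusion. The finding rests on the article alone and assumes that sites follow Table 5 as printed. It makes no claim about which instrument was intended.

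**What to change.** 1. The sponsor confirms which quality-of-life instrument was intended.
2. If EQ-5D and SF-12 are confirmed, as the agreement of Table 1, the outcome text and Table 5 suggests, replace AFEQT by EQ-5D and SF-12 in the statistical section. State that 12-month scores will be compared between groups by analysis of covariance with the baseline score as covariate. This is a change of wording and needs no new questionnaire or visit.
3. If the AFEQT was intended, add it to Table 1, to the outcome definition and to Table 5 without delay, because no visit currently schedules it. State also whether its comparison uses baseline. In that case, say how EQ-5D and SF-12 will be analysed, since they remain listed outcomes. This route adds a questionnaire at the visits chosen and a protocol change. If baseline is to be used, patients who enrol before the change will lack that value.

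On either route, make the outcome text and the statistical section describe the same contrast.
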